## Abstract

**Introduction:** With an increasing number of China's aging population, Parkinson's disease (PD) increases year by year. Persons with PD exhibit abnormal balance functions, leading to motor skills difficulties, such as unstable walking or even falling. Therefore, activities of daily living and quality of life are affected. This study aims to explore the effectiveness of Tai Chi training based on the mobile phone app in improving the balance ability of persons with PD.

**Methods and Analysis:** A randomized, single-blind, parallel controlled trial will be conducted in this study. One hundred forty-four persons with PD who meet the inclusion criteria will be randomly divided into a 1:1:1 ratio: (1) control group, (2) basic experimental group (basic app with no Tai Chi training features), and (3) balanced-enhanced experimental group (basic app with Tai Chi training features). Individuals with PD will be evaluated on balance and motor function outcomes. The primary outcome measure is the limits of stability (including the maximum excursion and direction control); the secondary outcome measures include the Unified Parkinson's Disease Rating Scale III (UPDRS-III), Berg Balance Scale (BBS), Functional Reach Test (FRT), Timed Up & Go (TUG), 6-Minute Walk Test (6MWT), and 39-item Parkinson's Disease Questionnaire (PDQ-39). Each group of patients will go through an assessment at baseline, 17 and 33 weeks.

**Discussion:** This study will evaluate the effectiveness of the mobile phone app Tai Chi training on the balance function of persons with PD. We assume that a challenging Tai Chi project based on a mobile phone app will improve balance in the short and long term. As walking stability progresses, it is expected that daily activities and quality of life improve. These findings will be used to improve the effectiveness of future home management measures for persons with PD.

**Ethics and Dissemination:** This study has been approved by the ethical review committee of the Shanghai University of Sport (approval number: 102772019RT056). Informed consent will be obtained from all participants or their guardians. The authors intend to submit the study findings to peer-reviewed journals or academic conferences to be published.

**Clinical Trial Registration:** Chinese Clinical Trial Registry (ChiCTR2000029135).

## Background

Parkinson's disease (PD), a neurodegenerative disease, is the misfolding and accumulation of α-synuclein (α-Syn) in dopamine neurons, which cannot be degraded, leading to neuronal death (1, 2). Studies have shown that PD is still an incurable progressive disease (3, 4). The primary aim of therapy is to slow PD's progress, thus improving life quality and extending lifespan (5). A multi-center PD long-term longitudinal follow-up study showed that 34% of patients had balance instability and abnormal balance reflexes within 2 years from the diagnosis of PD, Hoehn–Yahr stage III. Fifteen years later after a follow-up on surviving patients, 92% complained of abnormal balance (6). Newly diagnosed unmedicated persons with PD exhibited abnormalities of postural sway (7, 8). As the disease progresses, persons with PD will inevitably gradually develop instability of balance, and even fall, leading to fractures and disability (9). Therapies that help to improve balance function of persons with PD include drug therapy, functional rehabilitation training, and surgical treatment (10, 11). Medopa and levodopa have an excellent effect on muscle rigidity and retardation, but they cannot alleviate nor partially relieve the PD patients' balance symptoms (12, 13). Moreover, the side effects of long-term medication and medical expenditure should be considered (14, 15). Deep brain stimulation (DBS) is a surgical treatment of movement disorders, such as PD (16). However, the application of DBS is controversial (17, 18). Therefore, persons with PD urgently need a safe, effective, and operable treatment to slow the disease's progression or adjuvant drug treatment.

As one of the non-pharmacological interventions, exercise has been shown to improve gait disturbance, abnormal balance, and fall frequency to assist PD treatment (19, 20). Data suggest that intensive exercise is more effective in controlling balance and gait for PD (21). However, the prevalence of elderly persons with PD using this exercise is very low. As a traditional Chinese martial art, Tai Chi is very popular among the elderly (22). Studies have shown that Tai Chi is a moderate-intensity aerobic exercise, which positively affects fitness and balance ability and prevents falling in older people (23). Long-term Tai Chi training enhanced the balance and stability of persons with PD (24), which may be related to Tai Chi, increasing the range of motion of various joints and improving nerves' ability to control joints (25). However, the traditional Tai Chi movement is complicated and challenging to learn; hence, memory loss of persons with PD hinders training's feasibility and effectiveness. Persons with PD mainly exercise in groups, which require a large venue and a fixed time (26). Moreover, traffic problems and time schedules to reach the training site are often the key factors restricting persons with PD. With the development of telemedicine technology, various chronic diseases have achieved home monitoring and management, laying the foundation for persons with PD to achieve home rehabilitation training (27, 28).

With the combination of information technology and health care, mobile medical apps have emerged. The US Food and Drug Administration defines them as mobile apps installed on smart mobile devices to promote health and prevent diseases (29). In recent years, mobile medical apps have achieved good results in chronic disease management and have gradually become an essential tool for managing chronic disease patients (30, 31). It may be the most promising method to support the treatment of patients with chronic disease (32). Mobile health is also used in PD. For example, ParkinsonNet in the Netherlands is a professional website that connects persons with PD and doctors, equivalent to “persons with PD Facebook” (33). The remote PERFORM system for persons with PD is used for monitoring and evaluation and manages the symptoms and changes of persons with PD (34). However, few interventions based on smartphone apps have been developed to guide PD persons' home rehabilitation training in China.

An expert team composed of occupational therapists, graphic designers, and information technology experts has developed a new app called “Shoupa” focused on balance ability. The app program can be downloaded from the WeChat Mini Program or Apple Store (https://apps.apple.com/cn/app/%E5%AE%88%E5%B8%95/id1451277034?l=en). The app contains explicitly six aspects of the management of persons with PD. As far as we know, the effectiveness of this kind of mobile phone app-based Tai Chi training has not been verified in PD.

Therefore, this study aims to verify the effectiveness of the mobile phone app-based Tai Chi training in PD. For these purposes, a single-blind randomized controlled trial (RCT) will be performed. We hypothesize that app-based Tai Chi training will improve balance ability, thereby improving daily living and the quality of life of patients with PD. Tai Chi training based on a mobile app can be done at home, so persons with PD can train at any time of the day at their convenience. Consequently, this study will evaluate the efficacy of mobile phone app combined with Tai Chi interventions.

## Materials and Methods

### Study Design and Setting

This study is a single-blind (evaluators), parallel, RCT. Participants will be randomly divided into a control group, a basic experimental group, and a balanced-enhanced experimental group. Assessment will be carried out by the Shanghai University of Sport assessors at baseline, 17 weeks (end of intervention), and 33 weeks (16 weeks after follow-up). The research flowchart is shown in Figure 1. Ethical approval has been given by the ethical review committee of the Shanghai University of Sport (approval number: 102772019RT056, trial registration in Chinese Clinical Trial Registry: ChiCTR2000029135). The study will be performed according to the Consolidated Standards of Reporting Trials (CONSORT) guidelines (35).

**Figure 1 F1:**
[figure not shown]
Trail flow chart.

### Participants and Recruitment

This study will recruit 144 eligible participants from the neurology clinic of Shanghai Tongji Hospital. Eligible persons with PD must meet the following inclusion criteria. The consort diagram of participant recruitment is shown in Table 1. We intend to distribute leaflets in the neurology clinic, and the neurologist will introduce and publicize the content of this study. Members of the research team will register participants interested in this training program and conduct corresponding screening evaluations. After the baseline assessment, eligible participants will be randomly assigned to one of three study groups.

**Table 1 T1:** Schedule for data collection, the process of the assessments per visits.

**Measures**	**Baseline (0 week)**	**Intervention period (1–16 weeks)**	**End of intervention (17 weeks)**	**Follow-up period (17–32 weeks)**	**Follow-up (33 weeks)**
Participants' characteristics	√				
Limits of stability (maximum excursion and directional control)	√		√		√
UPDRS-III	√		√		√
BBS	√		√		√
FRT	√		√		√
TUG	√		√		√
6MWT	√		√		√
PDQ-39	√		√		√
Adverse experiences^a^		√		√	
Combined medication^b^		√		√	

a *Adverse experiences: any adverse experiences at any visit during treatment sessions and 36 weeks will be monitored. The research team will review all trial protocols, monitor patient safety, and investigate any adverse events*.

b *Patients will be asked whether they have used other medications during the treatment. If they have used concomitant medications, then the type and dose of medication taken by them will also be recorded in detail*.

*UPDRS-III, Unified Parkinson's Disease Rating Scale III; BBS, Berg Balance Scale; FRT, Functional Reach Test; TUG, Timed Up & Go; 6MWT, 6-Minute Walk Test; PDQ-39, 39-item Parkinson's Disease Questionnaire*.

### Inclusion Criteria

(1) Primary PD following the standard suggested by the Clinical Diagnostic Criteria for Parkinson's Disease in China (2016) (36);(2) Age of 50–70 years;(3) Meet the modified Hoehn–Yahr clinical grading criteria 1–2.5;(4) In stable condition with an essential dosage of madopar; and(5) Voluntary cooperation when training and signing the consent form.

### Exclusion Criteria

(1) Secondary PD;(2) Psychiatric conditions;(3) Severe medical diseases, such as severe heart, liver, and kidney diseases;(4) Speech or cognitive impairments; and(5) No other daily exercise history, no Tai Chi, or other rehabilitation training experience.

### Sample Size Calculation

Sample size calculations are based on the primary outcome measures of maximum excursion and directional control of limits of stability (LOS) measured using NeuroCom® Balance Master. Based on data provided by Li et al. (24), the primary outcome LOS was used to assess the maximum excursion and directional control in patients with PD (Cohen's *d* = 0.28, 15% improvement in maximum excursion, 12% improvement in directional control). For the current study, a similar effect size difference is anticipated between the balanced-enhanced experimental condition and the control condition. A smaller effect size difference is anticipated between the balanced-enhanced experimental condition and the basic experimental condition, hence the larger sample size. Based on sample size calculations (α = 0.05, β = 0.2), a total sample of 144 (assuming 15% attrition) will be sufficient to detect a small effect size (Cohen's *d* = 0.25) for between-group difference on the primary outcome if one exists.

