#### Primary Outcomes

The LOS is used to assess postural stability in this study. The LOS test requires each participant to intentionally displace the COG to their stability limits without losing balance. Reduced LOS can affect people's ability to complete activities of daily life that involve turning, leaning, or bending over (37) and has been associated with an increased risk of falls in several groups of patients, including the elderly and patients with neurological diseases, such as PD (38, 39).

We will assign a professional technician to perform the Balance Master® balance training tester (NeuroCom) to assess the LOS (40). These two factors will be included: (1) maximum excursion and (2) directional control.

The maximum excursion is a measure of stability. When the person tilts the body to the theoretical limit (100%) in each of the eight target directions without falling, the limit of active movement is evaluated. The average of the eight target directions (expressed as a percentage of LOS) will indicate the persons' maximum excursion during the task, and the higher percentage indicates the maximum degree of the excursion.

Directional control measures the body movement accuracy by comparing the linear distance to the desired direction (toward the target) and the persons' movement's actual path. Measurement results are expressed as a percentage (%), where a higher value indicates higher accuracy toward the intended target.

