### Statistical Analysis

Data will be analyzed in an open computing environment, R language, version 3.5.2. Differences between groups of baseline variables will be tested using the chi-square test (categorical variable) and one-way analysis of variance (continuous variable). Repeated measure ANOVA will be used to compare the changes from baseline to 16 weeks among the control group, basic experimental group, and balanced-enhanced experimental group. Pairwise comparisons between the balanced-enhanced experimental group and the two other groups will be conducted only if the omnibus F-test statistics indicated that the null hypothesis should be rejected. An independent sample *t*-test (95% confidence interval) will be used to compare group means. Paired *t*-tests will be used to examine changes within the groups from baseline to 16 and 32 weeks.

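### Two measures are primary under one alpha of 0.05 with no stated success rule: if either suffices alpha is exceeded, and if both are required the stated power is not met

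*Protocol article*

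**What the plan says.** All references are to the protocol article.

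- **Abstract:** one heading with two components. "The primary outcome measure is the limits of stability (including the maximum excursion and direction control").
- **Sample Size Calculation:** the plural. "Sample size calculations are based on the primary outcome measures of maximum excursion and directional control of limits of stability (LOS"). One pair of error rates follows, "Based on sample size calculations (α = 0.05, β = 0.2"), and the section closes in the singular: the sample is said to be "sufficient to detect a small effect size (Cohen's *d* = 0.25) for between-group difference on the primary outcome if one exists".
- **Primary Outcomes:** "These two factors will be included: (1) maximum excursion and (2) directional control". Each is then defined as its own percentage. One is the excursion averaged over eight directions; the other is the accuracy of the path to the target. No composite is formed.
- **Statistical Analysis:** "Repeated measure ANOVA will be used to compare the changes from baseline to 16 weeks" among the three arms. Comparisons of the balanced-enhanced arm with each of the other two "will be conducted only if the omnibus F-test statistics indicated that the null hypothesis should be rejected".

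No section ranks the two measures, splits alpha between them, or says whether one or both must be significant.

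**The concern.** The article moves between two primary outcomes and one, and attaches a single alpha and beta to them. The F-test gate shows that multiplicity was considered, but it works within one outcome. Each outcome has its own omnibus test, and nothing links the two.

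The Discussion expects the trial to show whether app-based Tai Chi should be advocated. If the two measures disagree, the present text does not say whether the trial has succeeded. The measure that reached significance could then be put forward after the results are known.

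**Working it through.** **Inputs.** Two primary measures, alpha 0.05, beta 0.2, 144 participants, 15% attrition and 1:1:1 allocation, all from the article. That is 48 per arm and 48 × 0.85 = 40.8, about 41 completers per arm. The correlation between the two scores is not given. Both come from the same test, so I take a range from 0 to 0.9.

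**The plan's own figure.** The article says "a total sample of 144 (assuming 15% attrition) will be sufficient" for Cohen's d = 0.25. Read literally as a two-group comparison, d = 0.25 needs 252 per arm, and 41 per arm gives about 20% power. The total of 144 is recovered only if 0.25 is read as Cohen's f for the between-group effect in a repeated-measures ANOVA with two time points and an unstated within-person correlation r = 0.5:

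- λ = f²·N·m / (1 + (m − 1)r) = 0.0625 × 120 × 2 / 1.5 = 10.0, giving 80.5% power at N = 120.
- 40 per arm / 0.85 = 47.06, rounded up to 48, and 3 × 48 = 144.

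The mismatch between d and f is a separate matter. Below I grant the article its 80% power on each measure.

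**Reading 1: either measure suffices.** With independent tests at 0.05, 1 − 0.95² = 0.0975. For correlated two-sided tests I used the bivariate normal. I also simulated three arms of 41 with one F-test per measure, followed by gated t-tests of Tai Chi against each other arm (global null, 100,000 runs per correlation).

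| Correlation | Either test, bivariate normal | Either omnibus F, simulated | Gated Tai Chi claim, either direction, simulated |
|---|---|---|---|
| 0 | 9.75% | 9.8% | 8.1% |
| 0.5 | 9.1% | 9.0% | 7.5% |
| 0.8 | 7.8% | 7.8% | 6.6% |
| 0.9 | 7.0% | 7.1% | 6.0% |

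A repeat calculation gave 6.7% for the gated claim at 0.8, so the last digit is within simulation error. The gate itself makes a Tai Chi claim on one measure somewhat conservative: 1 − √(1 − 0.081) = 4.1%. Counting only results that favour Tai Chi, the two-measure rate at correlation 0 is 4.2%, against 1 − √(1 − 0.042) = 2.1% for one measure. However the event is defined, a second unlinked measure nearly doubles the rate at correlation 0 and adds less as the correlation rises.

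**Reading 2: both measures are required.** The false-positive rate is at most 5%. For power, take 80% on each measure, so each test statistic has mean 1.960 + 0.842 = 2.802 and must exceed 1.960. The joint probability is 0.80² = 64% at correlation 0, 69% at 0.5 and 73% at 0.8.

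**Cost of a 0.025 threshold.** On the one reading that recovers 144, power at 122 completers is 81% at 0.05 and 73% at 0.025. Restoring 80% at 0.025 needs 144 completers. That is 48 / 0.85 = 56.5, rounded up to 57 per arm, or 171 in total.

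**The case against.** The strongest reply is that this is an omission. Multiplicity across outcomes is often left to an analysis plan, and a journal article is condensed. That would hold if the article were silent on multiplicity. Instead it states a rule that covers the arms and stops short of the two measures. It also states an alpha and a beta whose meaning depends on the missing success rule.

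A reader might infer that the plan lets success on either measure count at an uncorrected 0.05, and so that the false-positive rate is 9 to 10% instead of 5%. The documents do not support this:

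- No section states an either-or rule. The singular wording in the Abstract, and at the end of Sample Size Calculation, is compatible with requiring both.
- The 0.05 appears only as a sample-size input. That each measure is tested at 0.05 follows from the single alpha and the absence of any adjustment; it is not written.
- A rate of 9% or more also needs a correlation of no more than about 0.5, which the article does not give. For a gated Tai Chi claim, the rate stays below 9% even at correlation 0.

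Two further limits stand. The simulation uses a single F-test per measure, whereas a repeated-measures ANOVA has several terms and the article does not say which one is the gate. Nothing in the article ranks maximum excursion above directional control.

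**Conclusion.** The point holds in conditional form. Two measures are primary, one alpha and one beta are stated, the gate covers only the arms, and the success rule is not given.

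- If either suffices, the false-positive rate is above 5% and at most about 9.75%. The exact value depends on an unstated correlation.
- If both are required, alpha is safe. Joint power is then about 64 to 73% over correlations of 0 to 0.8, given 80% on each measure, so beta = 0.2 does not hold for that conclusion.

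Neither reading yields the stated alpha and beta together. This should be corrected, but it does not undermine the design and the repair is cheap.

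**What to change.** Pre-specify a fixed sequence. Test one named limits-of-stability measure first at 0.05, and the other at 0.05 only if the first is significant. The sponsor should choose the order before unblinding, for example maximum excursion first. Keep the F-test gate within each measure, and say that the sample-size statement applies to the first. This holds the error rate across the two omnibus tests at 5% or less and costs the first measure no power.

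The downside is that the second measure is tested only conditionally. If the first fails, no confirmatory claim can be made on the second.

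Two alternatives are valid but cost more. Holm across the two omnibus p-values needs the smaller one to be below 0.025. On the reading that recovers 144, that threshold takes power on a measure from about 81% to 73%, or the total from 144 to 171. Requiring both measures needs no change to alpha, but the sample size must then be justified for joint power.

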### Randomization and Allocation Concealment and Blinding

Randomization will be achieved through a random sequence table generated by a computer (Excel software; Microsoft). The subject's randomization will be carried out by a researcher who will not enroll the participants, assign them to their groups, or perform outcome measurements. The researcher will conceal the distribution in an opaque envelope, which can only be opened after the subject has completed the baseline assessment. The subjects will be randomly assigned to three groups (allocation ratio 1:1:1). Only the researcher responsible for guiding the use of the app can know how the participants are allocated. The researcher responsible for the follow-up reviews will be blinded to the distribution at any time during the data collection period. Moreover, the group assignment will be blinded to the assessors and data analysts.

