Nonetheless, there are some limitations in our trial. This is a single-center study, and the number of participants in our study is not large. The multi-center study design is expected to obtain a larger sample size in the future. Moreover, the lack of patient blinding may increase bias. Participants in the control group may reduce their participation, which will increase the difficulty of recruiting subjects. The number of interventions in the balanced-enhanced experimental group will be recorded automatically by the “Shoupa” app. Conversely, the actual adherence to the intervention needs to be confirmed and followed up by weekly telephone calls. The “Shoupa” app is expected to strengthen the function of video recording to monitor the training compliance of persons with PD.

Information gained from this project has the potential to influence the clinical decisions of doctors and will provide clear evidence as to whether app-based Tai Chi training should be advocated in people with PD. In conclusion, we expect that the presented app-based Tai Chi training in the patients' home-environment will be effective in balance ability.

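### The stated alpha, power, effect size (Cohen's d = 0.25) and N = 144 do not fit together: about 41 evaluable per arm gives about 20% power at that effect, not 80%

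*Protocol article*

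**What the plan says.** All of the claim stands in the protocol article, Sample Size Calculation.

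- Error rates: "Based on sample size calculations (α = 0.05, β = 0.2", that is, 80% power. Sidedness is not given.
- Sample size and attrition: "a total sample of 144 (assuming 15% attrition) will be sufficient to detect a small effect size".
- Effect size: Cohen's d of "0.25) for between-group difference on the primary outcome if one exists".
- Anchor from an earlier Tai Chi trial: Cohen's d of "0.28, 15% improvement in maximum excursion, 12% improvement in directional control". The section adds: "For the current study, a similar effect size difference is anticipated between the balanced-enhanced experimental condition and the control condition".
- Second contrast: "A smaller effect size difference is anticipated between the balanced-enhanced experimental condition and the basic experimental condition, hence the larger sample size".

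The section on randomization fixes equal arms: "The subjects will be randomly assigned to three groups (allocation ratio 1:1:1".

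The Statistical Analysis section plans a repeated measures ANOVA of change from baseline across the three groups. Pairwise comparisons of the Tai Chi arm with each other arm follow only if the omnibus F-test is significant, and independent-sample t-tests compare group means. The article gives no correlation between repeated measurements and no baseline covariate for the power calculation.

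**The concern.** The article prints every element of a power statement: alpha, beta, total N, attrition, allocation, effect-size metric and value. Such a statement can be checked as it stands, and 48 per arm is far too few for 80% power at a standardised difference of 0.25. This is not a complaint about missing detail. A fuller document could explain where 144 came from, but it could make the printed sentence true only by declaring a very high correlation.

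What is at stake is how a non-significant result is read. The Discussion says that the findings "will provide clear evidence as to whether app-based Tai Chi training should be advocated in people with PD". That sentence is not a power claim, but a reader who trusts the stated 80% would take a null result as evidence against a difference of 0.25. The comparison with the basic app arm is the more exposed of the two. It isolates the Tai Chi component, and the article itself expects the smaller effect there.

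**Working it through.** **Inputs.** From the article: alpha 0.05, power 80%, d = 0.25 (anchor 0.28), N = 144, 15% attrition, three equal arms. Assumed: a two-sided test, and a baseline to follow-up correlation r tried over a range.

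**Evaluable per arm.** 144 / 3 = 48; 48 × 0.85 = 40.8, about 41 (123 in total).

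**1. Trying to reproduce 144 with 0.25 as Cohen's d.** The normal approximation is n per arm = 2(1.960 + 0.842)² / d². At d = 0.25 this is 2 × 7.85 / 0.0625 = 251.2, so 252; the exact t calculation gives 253. Then 253 / 0.85 = 297.6, so 298 per arm, or 894 randomised. At d = 0.28 the exact figure is 202 per arm. The stated N is not reproduced.

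**2. Power of the pairwise t-test.** The noncentrality is d × √(n/2), with 2n − 2 degrees of freedom. For n = 41 and d = 0.25 it is 0.25 × √20.5 = 1.13.

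| Evaluable per arm | d = 0.25 | d = 0.28 | d detectable at 80% |
|---|---|---|---|
| 41 | 20% | 24% | 0.63 |
| 48 (no attrition) | 23% | 27% | 0.58 |

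A one-sided test at 0.05 with 41 per arm reaches about 30% at d = 0.25.

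**3. Omnibus F-test.** Cohen's f is the SD of the three arm means in units of the within-arm SD, and the noncentrality is N × f² with N = 123.
- Basic arm equal to control, means (0, 0, 0.25): f = 0.118, noncentrality 1.71, power 19%.
- Basic arm halfway, means (0, 0.125, 0.25): f = 0.102, noncentrality 1.28, power 16%.

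These apply to change scores only if their SD equals that of a single score, that is, at r = 0.5.

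**4. Comparison of change from baseline.** A change score has SD √(2(1 − r)) times that of a single score. A difference d at follow-up therefore becomes d / √(2(1 − r)), and the detectable d becomes 0.63 × √(2(1 − r)).

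| r | Pairwise power at d = 0.25, 41 per arm | d detectable at 80% |
|---|---|---|
| 0.3 | 16% | 0.74 |
| 0.5 | 20% | 0.63 |
| 0.7 | 30% | 0.49 |
| 0.8 | 42% | 0.40 |
| 0.92 | 80% | 0.25 |

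These figures ignore the omnibus gate, which can only lower them.

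**5. Readings that do return 144.** These are conjecture, because the article names no test, correlation or inflation rule.
- 0.25 as Cohen's f, between-groups test in a repeated measures ANOVA, three groups, two measurements, r = 0.5: noncentrality = N × f² × 2 / (1 + r). N = 117 gives 79.4% and N = 120 gives 80.5%. Then 40 / 0.85 = 47.06, rounded up to 48 per arm, or 144. Inflating the total instead gives 120 / 0.85 = 141.2.
- 0.28 as Cohen's f in a one-way ANOVA: N = 126, or 42 per arm; 42 × 1.15 = 48.3, about 48 per arm, or 144.
- Group-by-time test with f = 0.28 / 2 = 0.14, two measurements, r = 0.5: also N = 126, with the same result.

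In the first reading, f = 0.25 means a difference between the extreme arms of 0.25 / 0.471 = 0.53 (basic arm equal to control) or 0.25 / 0.408 = 0.61 (basic arm halfway).

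**The case against.** The strongest defence is that the lead analysis is a repeated measures ANOVA, not a simple t-test, and that such designs can be much more efficient. Entering f = d/2 = 0.125 as a group-by-time effect with two measurements and r = 0.7 does give about 90% power at N = 123. That input overstates the effect, however. A difference of 0.25 that appears only at follow-up produces interaction deviations half as large as the follow-up ones, so f is about 0.118 / 2 = 0.06 or 0.102 / 2 = 0.05. The equivalent pairwise comparison of change has 30% power at r = 0.7.

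A second objection stands in part. If 0.25 was Cohen's f, the planning effect was about d = 0.53 to 0.61, and a pairwise t-test with 41 per arm has about 66 to 78% power. A reader might therefore infer from the 20% figure that the trial is bound to miss its planning effect four times in five. The document supports that only if d = 0.25 is meant literally, and then at r = 0.5.

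A reader might equally infer that f was mislabelled as d and that this explains 144. The document does not establish that either. Several routes lead to 144, and this one does not explain why the anchor of 0.28 is also labelled as d.

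**Conclusion.** The power statement is wrong as written: its alpha, power, effect size and N are mutually inconsistent. With about 41 evaluable per arm and a two-sided test, power at d = 0.25 is about one quarter of what is claimed. At the stated attrition, 80% power would take about six times as many participants (894 / 144 = 6.2).

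Omitting attrition, testing one-sided or using the cited 0.28 does not close the gap. Only r near 0.92 would, and the article gives no such figure.

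The arithmetic is firm for d read as d. The exact power of the planned analysis depends on r, and the consequence for the trial depends on which metric the authors used. The conclusion is that the claim must be corrected, not that 144 is the wrong number to recruit.

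**What to change.** Keep N = 144 and replace the sentence with one along these lines:

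*With 144 randomised (about 41 evaluable per arm), the trial has 80% power at two-sided 0.05 for a pairwise between-group difference of about d = 0.63. For change from baseline the detectable difference is 0.63 × √(2(1 − r)), with r = [value and source]. Power at d = 0.25 is about 20% at r = 0.5.*

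State the effect-size metric, the test that the calculation refers to, its sidedness and the assumed correlation. The √(2(1 − r)) factor matches the planned comparison of change. The smaller ANCOVA factor √(1 − r²) should not be used unless an ANCOVA is planned: at r = 0.3 it would give 0.60 instead of 0.74.

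If 0.25 was Cohen's f, say so, give the equivalent d (about 0.53 to 0.61 between the extreme arms) and stop calling the effect small.

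The cost is protocol wording only. No participants are added, but the stated sensitivity of the trial becomes less favourable.
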